**Methods:**

We used the Behavior Change Wheel to develop an intervention for staff in primary care consisting of a 1-hour Internet-based eLearning package covering the links between obesity, type 2 diabetes, and the benefits of weight management, the treatment of diabetes in patients with obesity, specific training in raising the issue of weight, local services and referral pathways, overview of weight management components/ evidence base, and the role of the referrer. The package also includes a patient pamphlet, a discussion tool, a practice implementation checklist, and an optional 2.5-hour face-to-face training session. We have randomly assigned 100 practices in a 1:1 ratio to either have immediate access to all the resources or have access delayed for 4 months. An intention-to-treat statistical analysis will be performed.

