#### Step 3: Specify the Target Behavior

The target behavior, making “informed” referrals to weight management of patients with type 2 diabetes in primary care, needs to be performed by GPs and practice nurses, in the GP practice, during annual diabetes reviews, and during routine appointments if appropriate. The clinicians need to make more referrals to weight management, approach the subject sensitively and discuss it more often, encourage patients to take up referral and attend, and bring up the topic with patients more than once if required. They need to do this with every relevant patient (once a year per patient), working as a team between GP and nurse to decide who will do it.

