### Trial Design

A randomized trial design will be used for this evaluation with GP practices randomly assigned to one of the two arms described. We will notify clinicians of the STBD package and evaluation through primary care management, training forums, and communications. If interested, the practices will be able to opt in to the STBD evaluation via email. Once a practice has expressed interest, they will then be randomized to one of the two arms and either receive immediate access to the Internet-based training and print materials or receive access 4 months later (with awareness that their referral rates will be monitored).

The inclusion criteria for participants requires that they be GP practices in NHS Greater Glasgow and Clyde that have a contract for local enhanced services for long-term conditions (ie, diabetes) and have a unique clinical database (ie, not shared with another practice). Practices classified as “17c” (those with a separate NHS contract for long-term conditions) and those practices with a database shared with another practice (8 practices in area) are excluded.

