### Outcome Measures

The primary outcome is change in primary care referral rate to an adult NHS weight management service. Using data from the weight management database held by NHS Greater Glasgow and Clyde, the ratio of referrals over 3 months before and after the STBD intervention (allowing 1 month for completion) will be calculated. Secondary outcome measures include change in referral, including uptake ratio, local enhanced service template completion (weight management discussed); change in local enhanced service template completion; completion of lifestyle weight management phase (completion defined as 80% attendance); weight change (kg and %) in lifestyle weight management phase for those attending >1 session; and weight change (kg and %) at 1 year for all patients (data from annual diabetes review). Tertiary outcomes include diabetes medications at time of referral, that is percentage on weight gaining medications (sulphonylureas, thiazolidinediones, insulin), and percentage on weight neutral/reducing medications (GLP-1 agonists, metformin, DPP-IV inhibitors, SGLT2 inhibitors). Exploratory analyses (before and after) will be carried out to look at the effect of completion of training; change in referral rate analysis of those who completed Internet-based training only; when training done was completed by GP only, by practice nurse only or both; and change in referral rate in those where one practice member completed Internet-based plus face-to-face training.

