### Statistics

Comparisons between study arms will be by independent two-sample *t* tests or appropriate nonparametric equivalents using the prespecified comparisons.

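### Lifestyle-phase weight change and medication at referral are measured only in patients selected by referral or attendance, which the training aims to change, so arm differences can reflect case mix alone

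*Protocol article*

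**What the plan says.** Under Trial Design the article has "GP practices randomly assigned to one of the two arms described", and the abstract adds "We have randomly assigned 100 practices in a 1:1 ratio" and "An intention-to-treat statistical analysis will be performed". The primary outcome is the change in referral rate.

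Outcome Measures then lists several patient-level outcomes with different populations:

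- **Lifestyle-phase weight change:** "weight change (kg and %) in lifestyle weight management phase for those attending" more than one session.
- **Completion:** "completion of lifestyle weight management phase (completion defined as 80% attendance", with no denominator given.
- **1-year weight change:** described as covering all patients, with data from the annual diabetes review.
- **Medication:** "Tertiary outcomes include diabetes medications at time of referral", so it exists only for referred patients.

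The Discussion (Principal Considerations) describes the weight and medication outcomes as belonging to referred patients.

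On the aim of the training, Step 3 states "The clinicians need to make more referrals to weight management" and also asks clinicians to encourage uptake and attendance. On method, the Statistics section says "Comparisons between study arms will be by independent two-sample" t tests or nonparametric equivalents, using prespecified comparisons. It does not treat outcomes in selected patients separately.

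**The concern.** Referral and attendance happen after allocation and are the behaviours the intervention targets. If the training works, Arm 1's referred and attending patients will include people who would not have been referred under delayed access. The two arms' subsets then differ in composition even if the training changes no patient's weight or medication.

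The direction cannot be predicted. The article's description of the training (Step 8) has clinicians ask, assess and assist. A patient who sees weight as unimportant or lacks confidence is given support and a later discussion, while referral belongs to the assist step. The training may therefore bring in more hesitant patients, which would make Arm 1's attenders look worse. It may also screen on motivation, which would make them look better.

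What is at stake is the clinical reading. The Discussion says earlier training efforts have not been evaluated for their effect on referral and on patients' clinical outcomes. A difference in attenders' weight loss, under an intention-to-treat label, could easily be taken as that missing evidence.

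**Working it through.** The article gives no figure for this bias, so there is none to reproduce. The check is a mixture calculation under zero true effect.

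**Inputs from the article**
- Feasibility referral ratios R (Sample Size): 1.5 and 1.88. The counts reproduce them: 15/10 = 1.5 and 15/8 = 1.88. The section pairs the counts and ratios with opposite baselines, but only the size of R is used here.
- Background figures (Introduction): 5855 referred, 1537 attended assessment, 336 completed and lost at least 5 kg.

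**Assumed inputs**
- Control-arm referrals stay flat.
- D, the shortfall in weight loss of added attenders against usual attenders: 1 to 3 kg. The article gives no weight data to fix it.
- a, the attendance rate of added referrals relative to usual referrals: 1 or 0.5.

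**Step 1: share of added patients among Arm 1 attenders**

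Share = a(R − 1) / [1 + a(R − 1)]

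- R = 1.5, a = 1: 0.5/1.5 = 33%
- R = 1.5, a = 0.5: 0.25/1.25 = 20%
- R = 1.88, a = 1: 0.88/1.88 = 47%
- R = 1.88, a = 0.5: 0.44/1.44 = 31%

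**Step 2: spurious shift in mean loss among attenders = share × D**

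| R | a | D = 1 kg | D = 3 kg |
|---|---|---|---|
| 1.5 | 1 | 0.33 kg | 1.0 kg |
| 1.5 | 0.5 | 0.20 kg | 0.60 kg |
| 1.88 | 1 | 0.47 kg | 1.40 kg |
| 1.88 | 0.5 | 0.31 kg | 0.92 kg |

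If added attenders lose more rather than less, the sign reverses.

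**Step 3: medication at referral**

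All referred patients count here, so attendance does not enter. At R = 1.5, one third of any difference in medication use between added and usual referrals appears as an arm difference.

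**Step 4: why the denominator matters**

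Per referral, the background rate of completing with at least 5 kg loss is 336/5855 = 5.7%. If none of the added referrals succeeded, it would fall to 5.7%/1.5 = 3.8%, or 5.7%/1.88 = 3.1%. Successes per eligible patient would be unchanged. The same would apply to completion if it were taken per referral.

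**Step 5: the 1-year weight outcome**

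Outcome Measures assigns it to all patients; the Discussion assigns weight outcomes to referred patients. Under the first reading, taken as the whole eligible register, the population does not depend on allocation. Under the second it does. The article does not say which is meant.

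**The case against.** The best reply is that practices are randomised and that the article says patient data will be evaluated by practice (Identification of Participants and Consent). A practice's mean weight loss among attenders is then a post-randomisation practice-level summary, and a difference between arms is attributable to allocation, including its effect on case mix. This stands. A reader might infer that such comparisons have no basis in randomisation at all, and that would go too far. What fails is reading the difference as benefit or harm to patients. Practices with no attenders would also have no value.

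Other replies also carry weight:

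- A reader might infer that every patient-level outcome is confined to referred or attending patients. The 1-year weight outcome, as worded in Outcome Measures, is not.
- A reader might infer that completion is per referred patient. No denominator is stated, and a count per practice or per register is not excluded.
- A reader might infer that t tests on these subsets are certain. The list of prespecified comparisons is not shown, and the Trial Schedule names only the comparison of change in referral rate.
- Medication when a patient is referred may be meant as a marker of referral quality, since Table 1 mentions medication checks before referral. That is a legitimate descriptive use.
- The size of the shift depends on assumed D and a. If added patients are more hesitant, fewer will attend and the shift is smaller.

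None of this removes the selection in the two outcomes whose populations follow from the article's own definitions.

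**Conclusion.** The point holds in a limited form. Lifestyle-phase weight change and medication at referral are defined in patients selected by the behaviour the training targets. Arm differences in them mix a change in case mix with any effect on patients, in an unknown direction, and the intention-to-treat statement does not cure this. Completion is affected only if its denominator is referred or attending patients. The 1-year weight outcome is free of this selection only if it covers every eligible registered patient, and the two statements about it must be reconciled.

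For a 1.5-fold rise in referrals, the spurious shift in attenders' weight loss is 0.33 to 1.0 kg at equal attendance and 0.2 to 0.6 kg at half attendance. Both ranges rest on an assumed 1 to 3 kg gap and on flat control-arm referrals. They show what is possible and do not estimate the bias. The primary outcome, a practice-level referral measure, is unaffected. The consequence is a possible misleading secondary claim about clinical effect.

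**What to change.** Before the arms are compared on these outcomes:

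1. Compare arms by practice on the numbers attending and completing per eligible patient with type 2 diabetes on the practice register at randomisation. State the BMI threshold that defines eligibility: Step 2 gives at least 25 kg/m² for the target behaviour, while the Introduction counts patients at 30 or more.
2. Define the 1-year weight population as that same register population, and bring the Discussion into line.
3. State the completion denominator.
4. Report lifestyle-phase weight change and medication at referral by arm as descriptive, with no inference of a patient-level effect.

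The cost is mainly wording plus a register denominator. Linkage to weight management and diabetes records by practice is already planned.

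The real downside is dilution. The feasibility practices made 15/5 = 3 referrals each in three months. At the background attendance of 1537/5855 = 26%, that is about 0.8 attenders per practice. The register averages about 25,109/260 = 97 patients at BMI 30 or more, and would be larger at 25 or more. Effects per registered patient will be small. The 1-year weight contrast is weakened further because Arm 2 gains access at 4 months, and the report should say so.

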### Sample Size

A feasibility study was completed during which five practices (from a range of current referral rates to weight management services and deprivation areas in NHS Greater Glasgow and Clyde) were provided with access to the STBD e-learning program in June 2016. A GP and practice nurse from each attended a 2.5-hour face-to-face training session, and the practices were provided with the implementation toolkit. The referral rate to uptake was assessed for the 3 months prior to the STBD training (March-May 2016), 3 months post- STBD training (October-December 2016), and the same 3 months in 2015 (October-December 2015). We saw an increase in referrals of 50% compared to same period the year before (n=8 and 15 referrals respectively) and 88% compared to previous 3 months (n=10 and 15 referrals respectively) after the STBD intervention. Two practices did not make any referrals in the immediate time period analyzed prior to the intervention. As a result of this, together with the small number of feasibility practices, it was difficult to make a formal power calculation. The effect compared to same period 12 months before was 1.5 (SD 1.21); effect compared to 3 months previous was 1.88 (SD 0.38). A sample size of 80 per group would give 80% power to detect a difference of 0.5 in the change in referral rate based on a hypothetical SD of 1.12.

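### The pilot effects in the Sample Size section do not match their own counts, the planning SD of 1.12 has no stated source, and 50 practices per arm give about 60% power, not 80%

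*Protocol article*

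**What the plan says.** The Sample Size section describes a feasibility study in five practices, with referrals counted after training and in two earlier periods. For the first comparison it states: "We saw an increase in referrals of 50% compared to same period the year before (n=8 and 15 referrals respectively". For the second: "88% compared to previous 3 months (n=10 and 15 referrals respectively". It adds that two practices had no referrals in the period just before the intervention, and that this and the small number of practices made a formal power calculation difficult. It then gives the effects with SDs: "The effect compared to same period 12 months before was 1.5 (SD 1.21); effect compared to 3 months previous was 1.88 (SD 0.38". The size follows: "A sample size of 80 per group would give 80% power to detect a difference of 0.5 in the change in referral rate". The SD behind that figure is introduced with the words "based on a hypothetical SD of 1.12".

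The Outcome Measures section bases the primary outcome on the ratio of referrals in the three months after the intervention to those in the three months before. The Statistics section plans a two-sample t test or a nonparametric equivalent. The Results section reports that the trial was enlarged to 100 practices, 50 in each arm.

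**The concern.** Each printed percentage fits the other comparison's counts. The effects of 1.5 and 1.88 repeat the same pairing, so the slip appears twice and carries over to the SDs printed beside them. The pilot contrast that mirrors the primary outcome is the one against the preceding three months, and the text does not allow its effect or its SD to be identified.

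The SD actually used for planning is a third value with no stated origin. Finally, the 80% power is tied to 80 per group, and the article gives no power for the 50 per arm that were randomized. At stake are the stated rationale for the trial's size and the reading of a null result: a reader would take the power to be 80%.

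**Working it through.** **Pilot ratios** (counts from the Sample Size section)

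| Comparison | Counts | Recomputed | Printed |
|---|---|---|---|
| Same period a year earlier | 8 to 15 | 15/8 = 1.875, +88% | 1.5, +50% |
| Preceding three months | 10 to 15 | 15/10 = 1.50, +50% | 1.88, +88% |

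Exchanging the two printed effects restores agreement to the printed precision, so rounding is not the explanation. Two readings are open:

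- *The counts carry the right labels.* The three-months-before effect is then 1.50. Its SD is 1.21 if the SDs were exchanged together with the effects, and 0.38 if only the effects were.
- *The effects carry the right labels and the counts are exchanged.* The three-months-before effect is then 1.88 with SD 0.38, from 8 to 15 referrals.

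The SDs are not defined. If they describe the spread of practice-level ratios, the three-months-before SD can rest on at most 5 − 2 = 3 practices, because a ratio with a zero denominator does not exist.

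**Reproducing the stated size.** Inputs: difference 0.5, SD 1.12, power 80%, 1:1 allocation, two-sample t test. Alpha and sidedness are not stated; two-sided 5% is assumed.

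n per group = 2 × (1.960 + 0.842)² × SD² / difference²
= 2 × 7.849 × 1.2544 / 0.25 = 78.8, so 79 by the normal approximation. The exact noncentral t calculation gives 80, with 80.1% power. A one-sided 5% test would need 63, so the two-sided assumption is the one that fits. Neither the pilot counts nor the pilot percentages enter this formula.

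**Source of 1.12.** It is neither 1.21 nor 0.38. Their mean is (1.21 + 0.38)/2 = 0.80 and their root mean square is √((1.21² + 0.38²)/2) = 0.90, so it is not a simple average of them either.

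**Power for a difference of 0.5.** The noncentrality is 0.5 / (SD × √(2/n)):

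| n per arm | SD | Noncentrality | Power, exact t | Power, normal approx. |
|---|---|---|---|---|
| 80 | 1.12 | 0.5/0.1771 = 2.82 | 80.1% | 80.6% |
| 50 | 1.12 | 0.5/0.2240 = 2.23 | 59.9% | 60.7% |
| 80 | 1.21 | 0.5/0.1913 = 2.61 | 73.8% | 74.3% |
| 50 | 1.21 | 0.5/0.2420 = 2.07 | 53.4% | 54.2% |

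At SD 1.21, 80% power would need 93 per group (exact t).

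**The case against.** The strongest reply is that nothing in the sizing depends on the slip. The stated 80 per group uses only 0.5 and 1.12 and reproduces. The SD is openly labelled hypothetical, in a paragraph that concedes a formal calculation was difficult, so it need not equal a pilot SD. If the counts are labelled correctly, the contrast that matches the primary outcome is 1.50. Assuming no change in the control arm, that agrees with the planned difference of 0.5. Recruitment has closed, so corrected text alters neither design nor sample. All of this stands, and it limits the point to reporting, traceability and restated power.

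Three stronger readings are tempting, and the document does not support them:

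- A reader might infer that 1.12 is 1.21 with its digits exchanged. Nothing in the text shows this, and the word hypothetical points away from it. SD 1.21 therefore serves here only as a sensitivity value.
- A reader might set 11 per group (SD 0.38) against 93 (SD 1.21) and conclude that the required size is uncertain by that whole range. The plan was not sized on 0.38, and that SD may rest on three practices or fewer. If 1.21 were the right value, the change would be from 80 to 93.
- A reader might conclude that the sample-size inputs as a whole are unusable. The crossed figures are not inputs to the calculation.

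It can also be said that most of the lost power comes from randomizing 50 rather than 80 per arm, not from the pilot figures. That is correct: the fall from 80% to 60% occurs at the plan's own SD, and only the further step to 53% depends on the SD.

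**Conclusion.** The point holds in limited form. The pilot effects contradict their counts, and the article alone cannot show whether the counts or the effects are mislabelled. As a result, the effect and SD for the primary contrast cannot be identified. The planning SD lacks a stated basis. The calculation of 80 per group is sound on its own inputs.

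The consequence of size is that 50 per arm does not deliver the stated 80% power. For a difference of 0.5 it gives about 60% at SD 1.12 and about 53% at SD 1.21. The 80 per group would have had about 74% at SD 1.21. These figures assume a two-sided 5% t test with practices as the units and all 50 per arm analysed.

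**What to change.** 1. Recheck the data from the five feasibility practices and correct whichever of the counts or the effects is mislabelled, so that counts, percentages and effects agree for each comparison period. The correction should follow the data; the text does not settle its direction.
2. State what each SD measures, which comparator it belongs to, and how many practices it rests on.
3. Give the basis for the SD of 1.12.
4. Restate power for a difference of 0.5 at 50 per arm: about 60% at SD 1.12, with about 53% at SD 1.21 as a sensitivity value. Keep the 80-per-group figure only as the initial calculation, with its alpha and sidedness stated.

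The cost is a data check on five practices and a few corrected sentences. Neither the design nor the planned analysis changes.

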## Results

The first invitations for this evaluation were emailed in October 2017. Recruitment for this trial closed in April 2018. As there was an extremely large response to the single invitation email from the Primary Care Diabetes Lead sent in March 2018, to avoid discouraging willing practices we decided to extend the trial to include 100 practices (50 per arm). Follow-up is ongoing and linkage of practice data with referral data was completed by October 2018. It is expected that the trial will report in early 2019.

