### Limitations

One current limitation is the lack of a detailed process evaluation. We have some useful data available such as details of who has accessed the website and completed each of the modules, records of any requests for additional patient pamphlets or other materials, and full details of referral, uptake, and completion of weight management alongside electronic diabetes care records. If the intervention is not shown to be effective, it will be important to better understand what contributed to that lack of success, probably requiring interviews with practitioners and patients and even observation or recording of consultations.

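### The only stated power, 80%, belongs to 80 practices per group; with the 50 per arm randomised, the plan's own inputs give about 60%, and the article does not reconcile the two

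*Protocol article*

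**What the plan says.** The Sample Size section of the protocol article contains the only power statement: "A sample size of 80 per group would give 80% power to detect a difference of 0.5 in the change in referral rate". The SD behind this figure is 1.12, which the section itself labels hypothetical. Before this, the section says that a formal calculation was difficult, because the feasibility study had only five practices and two of them made no referrals in the period just before the intervention. It gives two pilot results: "The effect compared to same period 12 months before was 1.5 (SD 1.21); effect compared to 3 months previous was 1.88 (SD 0.38").

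The number randomised appears elsewhere. The Abstract (Methods) says: "We have randomly assigned 100 practices in a 1:1 ratio". The Results section says that, after a large response to an invitation email, "we decided to extend the trial to include 100 practices (50 per arm"). The Discussion also refers to 100 practices.

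The Statistics section names independent two-sample t tests or nonparametric equivalents. Under Trial Design, the unit of randomisation is the GP practice. The article states no alpha or sidedness and no allowance for loss of practices. It gives no power for 50 per arm, and Limitations mentions no shortfall.

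**The concern.** The two statements describe trials of different sizes. Practices are randomised and outcomes are evaluated by practice, so 80 per group means 160 practices. The trial has 100. Results presents 100 as an increase, while the only power calculation in the article makes it a reduction of 160 − 100 = 60 practices.

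A reader who takes the 80% at face value will think that a true difference of 0.5 would be missed about 2 times in 10. If the SD were 1.12, 50 per arm would miss it about 4 times in 10. That bears on how a non-significant result for the training package should be read. Recruitment closed in April 2018, so 50 per arm was known when the article appeared and the figure could have been restated.

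**Working it through.** **Inputs.** From Sample Size: difference Δ = 0.5, SD σ = 1.12, power 80%, 80 per group. From Abstract and Results: 100 practices, n = 50 per arm, 1:1. From Statistics: two-sample t test. Assumed, because the article does not state them: two-sided alpha 0.05 and no loss of practices.

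**Formula.** Noncentrality δ = Δ / (σ√(2/n)). Power is the probability that a noncentral t variable with 2n − 2 degrees of freedom and noncentrality δ falls beyond the two-sided 5% critical value.

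**Step 1: reproduce the plan's figure.**
- Normal approximation: n = 2(1.96 + 0.8416)² × 1.12² / 0.5² = 78.8, so 79 per group.
- Exact t test: 79 per group gives 79.6% and 80 per group gives 80.1%, so 80 per group are needed.
- At n = 80, δ = 0.5 / (1.12 × √(2/80)) = 0.5 / 0.1771 = 2.82.

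The stated 80 per group therefore reproduces. A one-sided 0.05 test would need only 63 per group and would have 87.8% power at 80, so it does not reproduce the figure. This supports the assumed two-sided 0.05.

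**Step 2: same inputs at the randomised size.**
- At n = 50, √(2/50) = 0.2 and δ = 0.5 / (1.12 × 0.2) = 0.5 / 0.224 = 2.23, against a critical t of 1.98.
- Power = 59.9% (noncentral t) or 60.7% (normal approximation).

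**Step 3: detectable difference at 80% power, n = 50.**
- Normal approximation: (1.96 + 0.8416) × 0.224 = 0.628.
- Exact t test: 0.634.

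Both round to 0.63, compared with the planned 0.50.

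**Step 4: sensitivity at 50 per arm, difference 0.5.**

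| Assumption | Power |
|---|---|
| SD 1.12, two-sided 0.05 (plan's inputs) | 59.9% |
| SD 1.21 (pilot, against same period a year before) | 53.4% |
| SD 0.38 (pilot, against previous 3 months) | over 99% |
| SD 1.12, one-sided 0.05 (does not reproduce the 80) | 71.6% |

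For 80% power at 50 per arm and a difference of 0.5, the SD would have to be about 0.88. The article does not give that value.

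**The case against.** The strongest reply is that the article promises little. It says that a formal calculation was difficult, calls the SD hypothetical, words the power conditionally, and reports 50 per arm openly. It never claims 80% power for 50 per arm, and it never says that 160 practices were required. The arithmetic in Sample Size is also correct as printed. All of this stands, and it means that the defect is an unreconciled inconsistency and not a miscalculation. But the hedging concerns uncertainty in the inputs. It does not explain why the size that the power refers to differs from the size randomised.

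A second reply is that the pilot SD of 0.38 comes from the comparison closest to the primary outcome, 3 months before against 3 months after, and would give over 99% power. This is fair as a warning against treating 60% as the true power. It does not show that the trial is well powered: there were at most five practices, two had no referrals in that earlier window, and the plan adopted 1.12 instead.

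Two stronger readings are tempting, and the documents do not support them.

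- From the word extend, a reader might infer that 80 was meant as the total. At 40 per arm the power would be about 50%, and the power sentence would itself be wrong. This remains only a possibility. The text says per group, that figure reproduces, and the original target may be in the full protocol, which is not shown.
- From the sentence "If the intervention is not shown to be effective, it will be important to better understand what contributed to that lack of success", a reader might infer a plan to treat a non-significant result as proof of ineffectiveness. That paragraph is about the missing process evaluation and the interviews or observation that might follow. It sets no rule for interpreting a test.

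**Conclusion.** The point holds as an inconsistency between Sample Size on one side and Abstract and Results on the other. The stated 80% power goes with 80 practices per group, and the trial has 50 per arm. Under the plan's own difference of 0.5 and SD of 1.12, power is about 60%, and the difference detectable with 80% power is about 0.63.

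This rests on a two-sided alpha of 0.05, which is assumed but reproduces the plan's figure, on a t test, and on no loss of practices. The 60% is the value at one hypothetical SD. It should not be read as the power the trial really has, because the two pilot SDs move it from about 53% to over 99% and neither is well founded.

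**What to change.** Change text only; enrol no further practices and leave the design and test as they are.

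- In Sample Size and Results, state the original recruitment target and the alpha and sidedness used, so that the 80 per group and the extension to 100 can be reconciled.
- Restate the power for the trial as randomised, for example: *100 practices (50 per arm) were randomised, giving about 60% power for a difference of 0.5 (SD 1.12, two-sided 5%), or 80% power for a difference of 0.63.* Keep the statement that the SD is hypothetical.
- Under Limitations, note the shortfall against 80 per group, so that a non-significant result is read with its confidence interval.

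The cost is a few sentences and a less favourable stated power.
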